## Abstract

**Background:**

Management of patients with bleeding oesophageal varices comprises of mainly diagnostic endoscopy, sclerotherapy and band ligation. One of the major problems to do any of the above is the active bleeding which makes any intervention difficult. The neuropeptide hormone somatostatin administered exogenously has caused a reduction in portal hypertension and variceal bleeding in patients suffering from liver cirrhosis. We believe that the symptomatic use of somatostatin for variceal bleeding in *Schistosoma mansoni *infected subjects can reduce bleeding, thereby alleviating the pathology caused by schistosomiasis.

**Methods/design:**

We herein present a study protocol for establishing this neuropeptide as a potential therapeutic agent in schistosomiasis. Adolescent subjects, age range varying from 12–17 years will be selected, based on several inclusion criteria, most important being infection with *Schistosoma mansoni *with bleeding from oesophageal varices in the last 24 hours. One group of schistosomiasis patients will be treated with somatostatin and praziquantel, the other with propanolol and praziquantel. Survival graphs will be set up to correlate somatostatin administration with survival time. A two part questionnaire will be set up to control treatment outcomes. The pre-treatment part of the clinical questionnaire will identify inclusion criteria questions, the post-treatment part of the questionnaire will identify treatment outcomes.

**Discussion:**

We expect that the administration of somatostatin as a bolus followed by a 24 hour long infusion, will stop bleeding immediately, delay rebleeding as compared to the control study group and delay mortality in the somatostatin treated subjects.

## Background

Complications due to severe schistosomiasis include fibrosis, hepatomegaly, splenomegaly, haematemesis, varices, portal hypertension, ascites formation and death [1]. Complications resulting from hepatic fibrosis (such as portal hypertension and variceal bleeding) are the principal cause of death in *S. mansoni *infected patients. In such patients portal hypertension leads to the formation of portal-systemic collaterals, specifically gastro-oesophageal collaterals (varices). Bleeding of these oesophageal varices can occur depending on the severity of fibrosis, and can be fatal. Praziquantel, the most commonly used anti-schistosomal drug, is effective against the worm stages of the parasite, but has no activity against the pathology (fibrosis) caused by the egg stages or the variceal bleeding that can be fatal in its outcome. These observations have stressed the need to combine praziquantel treatment with symptomatic treatment like with somatostatin.

Somatostatin is emerging as the ideal vasoactive drug for the control of variceal bleeding, and is as effective as sclerotherapy [2-4]. In a recent clinical trial, cirrhotic patients with acute bleeding of oesophageal varices were treated with infusion followed by bolus injections of somatostatin just before sclerotherapy. Results showed fewer treatment failures, fewer deaths or use of rescue therapy, reduced blood transfusion and less frequent, active bleeding. This drug also prevents recurrence and is free from any major side effects even when administered over prolonged periods of time.

We have studied the potential role of somatostatin in modulating *Schistosoma *caused morbidity. In endemic regions, at any given time, only a fraction of infected patients develop severe hepatic fibrosis. There may be a direct correlation between the development of severe fibrosis and the inability to generate required somatostatin levels. Our ongoing research at the Laboratory of Pathology give evidence to this fact, since somatostatin levels in Senegalese patients with severe morbidity (haematemesis, portal hypertension, variceal bleeding, ascites, fibrosis) are significantly lower than that in patients with no severe morbidity [5-10]. This effect indicates that somatostatin could be administered exogenously for therapeutic purposes in chronic schistosomiasis patients.

Complications linked to hepato-intestinal schistosomiasis are increasing in the area of Richard-Toll, Northern Senegal. These cases are being identified at the local health centre. However, considering the high prevalence of schistosomiasis in this region, it is likely that the number of severe cases is much higher. Clear guidelines for the management of such severe complications and criteria for referral and surgery are required in this region. The establishment of an algorithm on how to treat these patients and create the appropriate infrastructure is urgently needed. The priority is how to take care of these patients and more so what is the best way of doing this under local conditions. One of the first steps is to critically evaluate the Niamey-Belo-Horizonte ultrasound methodology in patients with severe periportal fibrosis. Efficient management of bleeding varices in the afflicted patients is imperative.

Given the background that somatostatin is an ideal vasoactive drug in the field of liver pathology, it is our opinion that somatostatin will be more efficacious and safe as compared to currently used beta blocker drugs like propanolol, in the control of acute oesophageal variceal bleeding due to *Schistosoma mansoni *infection. Moreover using this neuropeptide may increase time to failure of drug treatment, decrease incidences of early re-bleeding (day 4, 8) and incidences of death during the follow up period. Decreased frequencies of late rebleeding (days 30, 60, 90) may occur, all indicating the safety of using somatostatin. Praziquantel cover would be given to all study patients.

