#### 2. Treatment

Two groups of 10 schistosomiasis patients each will be identified. Group (1) will be treated with Somatostatin (3.5 μg/kg/hour; single bolus and i.v. infusion for 24 hours) + Praziquantel (40 mg/kg). For somatostatin treatment the i.v. infusion will be started first; 3 mg somatostatin will be dissolved in the 1 ml of saline provided. This solution will be added to the saline transfusion unit and administered to the patient for the next 12 hours. Once finished the second packet of 3 mg somatostatin will be used similarly for a second saline transfusion unit for the remaining 12 hours. The bolus dose of 250 μg will be dissolved in the 1 ml of saline provided and administered over 90 seconds soon after the start of the i.v. infusion.

Group (2) will be treated with Propanolol + Praziquantel.

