#### 3. Data analysis

Survival graphs will be set up to correlate somatostatin administration with survival time.

The primary efficacy variable is the number of patients meeting the failure of therapy definition during the infusion period. Failure criteria are defined as death during infusion, persistence of active bleeding (The haemodynamic instability criteria points to the inability to achieve and maintain a systolic blood pressure of 80 mm Hg OR presence of a 20 mmHg drop in systolic blood pressure from the highest post resuscitation value AND achieving a heart rate of 120 bpm OR a 20 bpm increase from highest post resuscitation value OR Inability to achieve and maintain a Hct of – 27% of Hb of – 9 g/dl despite blood transfusion of 2 units or more.

The clinical criteria of active bleeding include hematemesis (fresh or semi fresh blood), hematochezia, melena.

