#### 4. Control points

A two part questionnaire will be set up to control treatment outcomes. The pre-treatment part of the clinical questionnaire will identify inclusion criteria questions:

(1) When was the last haematemesis incidence?

(2) When did the present incident start?

The post-treatment part of the questionnaire will identify treatment outcomes. The following questions will be answered:

(1) What was the reaction to somatostatin infusion?

(2) When did bleeding stop after somatostatin infusion?

(3) GI disturbances: Is there abdominal pain, nausea, diarrhea, after somatostatin infusion?

(4) Control of early rebleeding: Is there early rebleeding in the 8 days following somatostatin administration?

(5) Control of late rebleeding: When is the next rebleeding incident? Subjects will be followed up on a monthly basis, by home visits.

(6) Control of mortality: Is there any difference in mortality time between the two groups.

(7) Control of fibrosis: Does ultrasonography detect anti-fibrotic effect of somatostatin after treatment?

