## Discussion

It is expected that the administration of somatostatin as a bolus followed by a 24 hour long infusion, will stop bleeding immediately, delay rebleeding as compared to the control study group and delay mortality in the somatostatin treated subjects. Our protocol that is based on a pilot study will help to establish the importance of somatostatin in schistosomiasis.

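### The Background hypothesis counts slower treatment failure and fewer rebleeds as evidence of safety, while the tolerability questions are put for somatostatin only

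*Protocol article*

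**What the plan says.** The Background of the protocol article states the hypothesis as an opinion: "it is our opinion that somatostatin will be more efficacious and safe as compared to currently used beta blocker drugs like propanolol". It goes on to say that the drug may "increase time to failure of drug treatment, decrease incidences of early re-bleeding (day 4, 8) and incidences of death during the follow up period", and closes the list with "Decreased frequencies of late rebleeding (days 30, 60, 90) may occur, all indicating the safety of using somatostatin".

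Other sections give the same outcomes a different role. Section 3, Data analysis, says: "The primary efficacy variable is the number of patients meeting the failure of therapy definition during the infusion period". The Discussion, like the Abstract, expects that somatostatin "will stop bleeding immediately, delay rebleeding as compared to the control study group and delay mortality in the somatostatin treated subjects".

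Tolerability appears only in section 4, Control points. Question 1 of the post-treatment questionnaire asks how the patient reacted to the somatostatin infusion. The other item reads "3) GI disturbances: Is there abdominal pain, nausea, diarrhea, after somatostatin infusion".

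On size, section 2, Treatment, says: "Two groups of 10 schistosomiasis patients each will be identified". The Sample Size Criteria in section 1 use assumed bleeding proportions only.

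**The concern.** A drug can postpone failure and reduce rebleeding and still do harm by another route. A good result on those outcomes says that the treatment works. It does not say that the treatment is well tolerated. The Background sentence is the only place in the article that says which results of this trial would indicate safety, and most of what it names is efficacy.

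The expectation is also comparative, with propanolol as the reference. A comparison of harms needs the same information from both arms, and the tolerability questions as worded do not provide it.

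What is at stake is the conclusion the trial may draw. The patients are 12 to 17 years old with bleeding varices. A favourable rebleeding result could be written up as a finding on safety although it contains little information about harm.

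**Working it through.** **Step 1. The role of each outcome named in the Background sentence.**

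| Outcome | Role elsewhere in the article | Can it show absence of harm? |
|---|---|---|
| Time to failure | Failure during infusion is the primary efficacy variable (section 3) | No |
| Early rebleeding (days 4, 8) | Expected treatment effect (Abstract, Discussion) | No |
| Late rebleeding (days 30, 60, 90) | Expected treatment effect (Abstract, Discussion) | No |
| Death | Part of the failure definition if during infusion (section 3); delayed mortality is an expected effect (Discussion) | In part: also a safety outcome |

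The inference fails for three of the four rows and is partly defensible for the fourth.

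**Step 2. The items that do bear on harm.** Questions 1 and 3 in section 4 both refer to the somatostatin infusion. As worded they yield no propanolol figure, so no difference between arms can be formed from them.

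**Step 3. What the sample size was built on.** The plan's figure is 10 per group. The article does not say which row of its grid this comes from; the row that shows 10 is 90% against 30% bleeding, with 80% power and alpha 0.05. The two-sided pooled formula without continuity correction has mean proportion 0.60 and difference 0.60:

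n = [1.96 × √(2 × 0.60 × 0.40) + 0.8416 × √(0.90 × 0.10 + 0.30 × 0.70)]² / 0.60² = (1.358 + 0.461)² / 0.36 = 9.2, rounded up to 10.

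The figure is reproduced (a two-sided Fisher exact test would need 12). It concerns bleeding; no harm rate enters it.

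**Step 4. What 10 exposed patients can say about harm.** The input is n = 10 on somatostatin (section 2).

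- Exact upper limit with 0 events, one-sided 95%: 1 − 0.05^(1/10) = 0.259.
- Exact upper limit with 0 events, two-sided 95%: 1 − 0.025^(1/10) = 0.308.
- Chance of seeing no event if the true rate is 10%: 0.90^10 = 0.349.
- Chance of seeing no event if the true rate is 5%: 0.95^10 = 0.599.

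The 5% and 10% rates are assumptions, since the article gives no harm rates.

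**Step 5. What 10 against 10 can say about relative harm**, supposing both arms were asked. With 0/10 on somatostatin, the two-sided Fisher p-values are:

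- 4/10 on control: 2 × C(10,4)/C(20,4) = 2 × 210/4845 = 0.087.
- 5/10 on control: 2 × C(10,5)/C(20,5) = 2 × 252/15504 = 0.033.

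At least half of the control patients would need the event before the difference reached 0.05. Power is 5.7% for an assumed 30% against 10%, and 15.2% for 40% against 10%.

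**The case against.** The strongest reply is that the sentence is not an analysis rule. It stands in the Background, is offered as opinion and is hedged. Data analysis draws no safety conclusion, and the trial calls itself a pilot. All of that stands, and it is why the point is minor.

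A reader might infer that the trial would declare somatostatin safe on rebleeding results no matter what adverse events occurred. The article does not support this. Nothing in it says that adverse events are to be disregarded, and section 4 collects some of them as treatment outcomes. A reader might also take the Discussion to promise a safety finding. It speaks of the importance of somatostatin, not of its safety.

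Three further points are fair:

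- Death is legitimately a safety outcome as well, so part of the sentence is defensible.
- The comparative phrase is loosely built and may not mean strictly safer than propanolol.
- The limits in steps 4 and 5 hold for any 10 patients. They do not measure the error of reading efficacy as safety; they show only that a sample of this size could not rescue the claim.

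It could also be said that adverse-event analysis belongs in a fuller protocol or analysis plan that is not shown. That is right, and no missing safety analysis is alleged. What remains is a statement on the page that is wrong for failure and rebleeding, and two questions whose wording excludes the comparator.

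**Conclusion.** The concern holds in limited form. Time to failure and rebleeding are efficacy outcomes by the article's own description and do not indicate safety; death bears on both. The tolerability items are not linked to the safety inference and, being worded for one arm, cannot support a comparison with propanolol.

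On size, no events in 10 patients would leave true rates up to 25.9% (one-sided 95%) or 30.8% (two-sided 95%) open. This rests only on 10 patients being treated and observed independently. The miss probabilities (35% and 60%) and the power figures rest on assumed event rates.

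Severity is minor: no endpoint, sample size or decision rule changes, but the conclusions the trial may draw do.

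**What to change.** 1. In the Background, delete the closing clause that presents these outcomes as indicating safety.
2. Describe failure and rebleeding as efficacy outcomes, and death as a clinical outcome relevant to both efficacy and safety.
3. In section 4, reword questions 1 and 3 so that they ask about reactions and gastrointestinal symptoms after study treatment in both arms, and report the answers by arm with exact confidence limits.
4. State that, with 10 patients exposed, the pilot will describe harms and make no claim of safety or of superior safety to propanolol.
5. Do not count heart rate and blood pressure changes that already form part of the failure criteria in section 3 as separate safety evidence; that would repeat the overlap.

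The cost is a few changed sentences, a little more questionnaire work in the control arm, one small table and a less favourable claim. No extra patients are needed and treatment is unchanged.

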### Study design

#### 1. Selection of patients

Age and Morbidity criteria – Adolescent subjects, age range varying from 12–17 years will be selected. The inclusion criterion will be schistosomiasis patients with bleeding from oesophageal varices in the last 24 hours. A random selection will be made to form two groups, a study group and a control group. Control of active infection will be done by means of CAA-strips on urine or blood. Subjects will be asked to fill in an informed consent form and the pre-treatment part of a questionnaire.

The inclusion criteria will be established fibrosis due to schistosomiasis of clinical history, physical examination and laboratory findings (and an examination compatible with the presence of portal hypertension due to fibrosis). Clinically active upper gastrointestinal bleeding (haematemesis of fresh or semi fresh blood and/or melena and/or haematochezia) with or without haemodynamic instability (systolic blood pressure < 80 mm Hg and heart rate > 120 bpm) will be selected. Subjects must be male or non-pregnant, non-lactating female subjects. Females of childbearing potential will have to utilize contraception for the duration of the study. Written or verbal documented informed consent will be needed from all subjects.

Exclusion criteria will include participation by subjects in another investigational study within the last 14 days. Subjects may not undergo treatment with endotherapy, i.e. band ligation, sclerotherapy or other (balloon tamponade). Treatment with somatostatin, vasopressin or their analogues will also be a exclusion criteria. Subjects with end stage liver disease with hepatorenal syndrome, diffuse hepatocellular carcinoma, patent porto-systemic shunts, known diagnosis of non-fibrotic portal hypertension, severe cardiovascular diseases, i.e. acute myocardial infarction and heart failure will be excluded. Concurrent use of metoclopramide is also not advised.

Conduct of trial – Active bleeding episode (haematemesis, haematochezia, melena) from a potential variceal source should be confimed by a medical team (the ER physician, the ICU physician, the investigator). Patients may be outpatients or already hospitalised patients. Patients will be randomised to either arm in a sequential manner. Randomisation, and the start of study drug infusion if in adjunctive therapy arm, should be accomplished as soon as possible following identification of a patient qualifying for the study and following the conduct of pre-randomisation study procedures.

Sample Size Criteria – Assuming a 80% chance of finding a significant difference <0.05 between the two study cohorts, the following statistics were established:

(A) If 99% of the untreated subjects and –

10% of somatostatin treated subjects bled -5 volunteers per group were sufficient;

20% treated subjects bled – 7 volunteers per group were required;

30% treated subjects bled-9 volunteers per group were needed.

(B) If 90% of untreated subjects bled, and –

10% of somatostatin treated group bled – 7 volunteers in each cohort were sufficient;

20% of somatostatin treated group bled – 9 volunteers in each group were required;

30% of somatostatin treated group bled – 10 volunteers in each group were needed.

(C) If 70% of untreated subjects bled, and:

10% of somatostatin treated group bled – 12 volunteers per group were sufficient;

20% of somatostatin treated group bled – 18 volunteers per group were required;

30% of somatostatin treated group bled – 28 volunteers per group were needed.

In cirrhotic patients with bleeding oesophageal varices somatostatin administration controls bleeding in more than 80% of the treated patients. Based on this report, we propose to start this pilot study with 10 subjects/group.

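### Bleeding patients with systolic pressure below 80 mm Hg may be randomised to a beta blocker, and no printed criterion defers those who are still hypotensive

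*Protocol article*

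**What the plan says.** Under **1. Selection of patients**, the protocol article takes patients with clinically active upper gastrointestinal bleeding "with or without haemodynamic instability (systolic blood pressure < 80 mm Hg and heart rate > 120 bpm) will be selected". Instability is therefore no bar to entry.

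Under **2. Treatment**, the control arm is set in one line: "Group (2) will be treated with Propanolol + Praziquantel". No haemodynamic condition is attached. The **Background** places the drug in its class and gives its purpose, comparing somatostatin with "currently used beta blocker drugs like propanolol, in the control of acute oesophageal variceal bleeding due to" *S. mansoni* infection.

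The exclusion list has one item relevant to a beta blocker: "severe cardiovascular diseases, i.e. acute myocardial infarction and heart failure will be excluded". The conduct paragraph of the same section asks for randomisation without delay, "following identification of a patient qualifying for the study and following the conduct of pre-randomisation study procedures", but does not list those procedures.

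Under **3. Data analysis**, blood pressure and heart rate return in the failure definition: "the inability to achieve and maintain a systolic blood pressure of 80 mm Hg" and "achieving a heart rate of 120 bpm OR a 20 bpm increase from highest post resuscitation value".

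**The concern.** A randomised comparison is safe only if every eligible patient can reasonably receive either treatment. Here the eligibility rule admits patients who are hypotensive and tachycardic from blood loss, and one of the two arms is a beta blocker. If such a drug lowers pressure further or blunts the heart-rate response (drug-class knowledge, which the article does not state), these patients are poorly suited to one arm. They are also only 12 to 17 years old.

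If the treating team instead withholds or delays propranolol, an unstable control patient has no acute study drug for part or all of the 24-hour infusion period over which the primary endpoint is counted, while an unstable patient in Group 1 receives somatostatin. The printed rules choose neither course.

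There is a secondary link to the endpoint, because the drug may act on two of the quantities that define failure.

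**Working it through.** No arithmetic applies. The check is to follow one patient through the printed rules.

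1. **Presentation.** A patient has active haematemesis, systolic pressure below 80 mm Hg and heart rate above 120 bpm. This is exactly the article's definition of haemodynamic instability, and the inclusion sentence accepts it.

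2. **Exclusions, item by item.**
   - Another investigational study in the past 14 days: does not address hypotension.
   - Endotherapy or balloon tamponade: does not address it.
   - Somatostatin, vasopressin or analogues: does not address it, and beta blockers are not named.
   - End-stage liver disease with hepatorenal syndrome, diffuse hepatocellular carcinoma, patent porto-systemic shunts, known non-fibrotic portal hypertension: none is a haemodynamic criterion.
   - Severe cardiovascular disease: limited by its wording to two named conditions. It cannot be stretched to hypotension from bleeding, which the same section expressly admits.
   - Concurrent metoclopramide, advised against: does not address it.

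3. **Before randomisation.** Unlisted procedures must be completed. They may or may not include a blood pressure check. No stabilisation requirement is printed.

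4. **Allocation.** The patient may be assigned to either group. If Group 2, the assigned drug is propranolol, with no minimum blood pressure.

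The instability definition joins its two parts with *and*. A patient with systolic pressure below 80 mm Hg and heart rate of 120 bpm or less is not unstable by that definition, yet is equally hypotensive and equally eligible. A screen should therefore rest on pressure alone.

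**Effect on the endpoint.** A further fall in pressure would move a control patient towards the failure threshold. A drug-induced fall in heart rate could keep the heart-rate part of the definition from being met and so move the patient away from failure. The two effects oppose each other, and the article gives nothing from which to weigh them. The direction of any bias cannot be derived.

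**The case against.** The strongest reply is that this is a condensed article. It says the exclusions *include* the listed items, so the list need not be complete, and the unlisted procedures before randomisation could contain a blood pressure check. Contraindications, dose and start time of propranolol commonly sit in the full protocol. As far as dose and schedule go, this stands, and their absence is not the point. But the inclusion sentence is not silent on instability: it expressly makes it eligible, and the control drug is assigned without condition. The point concerns two printed rules taken together.

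A reader might infer that the protocol orders propranolol for patients in shock. The documents do not support that. No start time is printed for propranolol, the instruction to begin quickly refers to randomisation and to a study drug infusion, and the failure definition refers to values after resuscitation and to transfusion, so resuscitation is presupposed. What the text permits is allocation; it does not say when the drug is given.

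A reader might also infer a bias in a known direction, or argue that in groups of 10 a single such patient could change the result. The first is not derivable, as shown above. The second holds for any patient whose outcome changes for any reason, so it does not measure this defect.

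It is also fair to say that harm from a beta blocker in hypotension is outside the documents, which present the class as in current use for acute variceal bleeding. The premise is therefore stated as an assumption.

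Finally, if the remedy were a clinician's judgement that the patient is fit for either drug, it could invite selection, since allocation is described as sequential and might be guessed. That objection is accepted and shapes the fix.

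**Conclusion.** The point holds in a limited form and should be fixed. The printed rules make patients with systolic pressure below 80 mm Hg and heart rate above 120 bpm eligible, allow them to be randomised to a beta blocker, and contain no criterion that defers those who are still hypotensive.

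The case rests on patient safety and on one assumption, that a beta blocker can worsen hypotension. How many patients are affected is unknown, because the article gives no share of unstable patients. The size and direction of any endpoint bias are also unknown, and no number is offered for them. If the full protocol already contains a stabilisation step, the remedy is only to bring the inclusion sentence into line with it.

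**What to change.** Amend the inclusion sentence to read:

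> *with or without haemodynamic instability at presentation, provided that after initial resuscitation and before randomisation systolic blood pressure is at least 80 mm Hg*

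Record the value before allocation, apply the condition identically to both arms, and list it among the procedures before randomisation. Under **2. Treatment**, add that propranolol is not started or continued while systolic pressure is below 80 mm Hg. The limit is the article's own threshold; because it uses pressure alone, it also covers hypotensive patients whose heart rate is 120 bpm or less. The gate should be this measured value and not a team's opinion, for the selection reason given above.

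**Cost.** Two sentences and one recorded measurement, plus three consequences to accept openly:

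- Randomisation, and with it somatostatin, is delayed or lost for some unstable patients.
- Patients who never reach 80 mm Hg leave the population, so the part of the failure definition about *achieving* that pressure will rarely apply. The part about *maintaining* it remains.
- A control patient who falls below 80 mm Hg after allocation goes without propranolol for that time.

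The alternative is to leave eligibility as it is and add only the rule on withholding propranolol. That avoids delaying somatostatin, but leaves every control patient who enters hypotensive without acute study drug until pressure recovers. The condition before randomisation is preferable because it treats both arms alike.

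### The sample-size table gives 10 per group for 90% v 30% bleeding but 12 for its mirror image, 70% v 10%; the rest of the table points to 12 for both.

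*Protocol article*

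**What the plan says.** In the Protocol article, Study design, section 1 (Selection of patients), the Sample Size Criteria open with a single rule: "Assuming a 80% chance of finding a significant difference <0.05 between the two study cohorts". Nine scenarios follow in three blocks, with 99%, 90% and 70% of untreated subjects bleeding, each set against 10%, 20% and 30% of somatostatin-treated subjects.

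- Block B begins "If 90% of untreated subjects bled" and ends with "30% of somatostatin treated group bled – 10 volunteers in each group were needed".
- Block C begins "If 70% of untreated subjects bled" and its first row is "10% of somatostatin treated group bled – 12 volunteers per group were sufficient".

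The section then cites control of bleeding in more than 80% of treated cirrhotic patients and concludes: "Based on this report, we propose to start this pilot study with 10 subjects/group". It names no test, formula or sidedness for the table.

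**The concern.** Comparing bleeding rates of 90% and 30% is the same as comparing non-bleeding rates of 10% and 70%. With equal groups, a test that treats event and non-event alike cannot need 10 per group for one and 12 for the other at the same power and significance level. At least one entry is therefore wrong.

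If the wrong one is 90% v 30%, its value happens to equal the adopted group size. As printed, 10 per group covers all three rows of the 90% block. As corrected, it covers only two. A reader would wrongly conclude that the pilot still has 80% power if 30% of somatostatin patients bleed.

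**Working it through.** **Inputs.** From the Sample Size Criteria: power 80%, significance 0.05, equal groups, and the nine pairs of rates with their stated sizes. Assumption: a two-sided test, because sidedness is not stated.

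**Step 1: formula.** Pooled-variance formula for two proportions, with d = p1 − p2 and p̄ = (p1 + p2)/2:

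n₀ = [1.960·√(2p̄(1−p̄)) + 0.8416·√(p1(1−p1) + p2(1−p2))]² / d²

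Continuity-corrected: n = (n₀/4)·[1 + √(1 + 4/(n₀d))]²

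**Step 2: reproduce the table.**

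| Untreated v treated | Stated | Uncorrected n₀ | Corrected n | Smallest n for 80% power, two-sided Fisher |
|---|---|---|---|---|
| 99% v 10% | 5 | 3.42 | 5.44 | 5 |
| 99% v 20% | 7 | 4.67 | 6.97 | 7 |
| 99% v 30% | 9 | 6.22 | 8.88 | 9 |
| 90% v 10% | 7 | 4.75 | 7.02 | 7 |
| 90% v 20% | 9 | 6.61 | 9.25 | 9 |
| **90% v 30%** | **10** | **9.19** | **12.30** | **12** |
| 70% v 10% | 12 | 9.19 | 12.30 | 12 |
| 70% v 20% | 18 | 14.30 | 18.08 | 18 |
| 70% v 30% | 28 | 23.31 | 28.09 | 29 |

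Rounded to the nearest integer, the corrected formula matches eight of nine entries. Fisher's test agrees, apart from a difference of one in the last row (79.0% power at 28).

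**Step 3: the two mirror rows in full.** For 90% v 30%, p̄ = 0.6, 2p̄(1−p̄) = 0.48, and 0.09 + 0.21 = 0.30. For 70% v 10%, p̄ = 0.4, 2p̄(1−p̄) = 0.48, and 0.21 + 0.09 = 0.30. In both, d = 0.6. Hence in both:

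n₀ = (1.3579 + 0.4610)² / 0.36 = 9.19

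n = (9.19/4)·(1 + 1.3136)² = 12.30

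**Step 4: can another method give 10?** Yes, several can for 90% v 30%:

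- uncorrected two-sided: 9.19, rounded up to 10;
- one-sided continuity-corrected: 10.18;
- one-sided Fisher: 10 (power 82.4%).

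Variants with unpooled variance (two-sided, corrected: 9.58) or the arcsine transform (one-sided, corrected: 9.95) also round to 10. Each gives the same value for 70% v 10%, where the table says 12, and none fits the rest of the table. For 70% v 20% and 70% v 30% (stated 18 and 28), the first three give 14.3 and 23.3, 14.9 and 23.0, and 15 and 23.

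**Step 5: power at 10 per group.** Exact binomial power, two-sided Fisher test at 0.05, 90% bleeding in the untreated group:

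| Somatostatin bleeding rate | Power at n = 10 |
|---|---|
| 20% | 84.1% |
| 22% | 81.0% |
| 23% | 79.3% |
| 30% | 66.7% |

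For 90% v 30%, power is 75.5% at 11 per group and 82.6% at 12.

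**The case against.** **The power figure depends on the test.** The article names none. At 10 per group and 90% v 30%, an uncorrected two-sided chi-square has exact power of 82.4%, against 66.7% for two-sided Fisher or the Yates-corrected chi-square. This stands. The 67% must carry the name of its test, and the choice of test is inferred from the other eight rows. The conflict between 10 and 12 needs no such inference.

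**The size of the trial was not taken from this row.** A reader might infer that the faulty entry drove the choice of 10 per group, since the numbers coincide. The text does not support that. It rests the choice on control in more than 80% of treated patients, so on about 20% or fewer bleeding. The matching row at 90% untreated bleeding is 90% v 20%, stated as 9. That row is right: 9.25 by formula, and Fisher power of 83.0% at 9 per group. This objection also stands.

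**The article does not claim that 10 is enough everywhere.** Block C shows 12, 18 and 28, and the study is called a pilot. A reader might infer that the article hides a general lack of power, but these rows show openly where 10 falls short. The error conceals one further scenario.

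None of these points explains how 10 and 12 can both follow from one rule.

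**Conclusion.** The 90% v 30% entry is wrong by 2 per group: 12 under the table's own rounding to nearest, or 13 if rounded up, against the stated 10. That the two mirror entries conflict follows for any test symmetric in event and non-event. That 90% v 30% is the faulty one rests on the two-sided continuity-corrected formula, which reproduces every other entry; two-sided Fisher supports it.

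On the two-sided Fisher test, 10 per group falls about 13 points short of the stated 80% in this scenario (66.7%). The consequence is limited: coverage of the 90% block becomes less favourable, while the stated basis for 10 per group and the 90% v 20% row remain sound.

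**What to change.** In block B of the Sample Size Criteria, change the 90% v 30% entry from 10 to 12 per group (13 if rounding up). Add one sentence: with 10 per group and 90% bleeding in untreated subjects, two-sided Fisher exact power is about 84% if 20% of somatostatin patients bleed and about 67% if 30% do, falling below 80% above about 22%.

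The cost is one number and one sentence. This point does not require a change to the pilot's size; the stated power for one scenario becomes less favourable.
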